## Abstract

**Background:**

Self-exercises focusing on strength and endurance training, as well as self-mobilization, are effective in neck pain (NP). This study aims to investigate the differences in self-management using two workplace-based interventions: a smartphone application consisting of personalized neck exercises compared to conventional approach (self-exercises program on paper) in chronic NP office workers.

**Methods:**

The project is a prospective, superiority, randomized controlled trial. Fifty participants with chronic NP will be randomly assigned into the interventional group (IG, n = 25), utilizing the smartphone application, or the control group (CG, n = 25). The CG includes the use of a paper sheet with exercises and recommendations, and the IG includes the use of a smartphone application, which provides individualized exercise programs. Both protocols will last three months and will be preceded by an educational session at baseline for all participants. The main outcome measure comprises pain intensity evaluated according to the pain intensity number rating scale. Secondary outcomes are function evaluated according to the neck disability index, quality of life according to the short form 12, and participants’ adherence to self-exercises. Outcome measures will be collected at baseline, and one and three months of follow-up.

**Discussion:**

The current project will evaluate the effectiveness of a smartphone application consisting of personalized neck exercises, when compared with a conventional approach for self-rehabilitation. The smartphone application will allow to monitor the participants’ status and to help resolving the problem of adherence to self-exercises in chronic NP. Despite some limitations may be related to the short follow-up duration, the study findings could help to develop evidence-based knowledge about the impact of workplace interventions using new technologies in mitigating discomfort and promoting well-being among affected workers.

**Trial Registration:**

ClinicalTrials.gov. NCT06485804 Registered on July 1, 2024.

## Introduction

### Background and rationale

Professional organizations worldwide are increasingly recognizing the importance of investing in quality assurance measures aligning closely with international standards that emphasize not only the quality of products and services [1], but also the quality of work life (QoWL) [2]. The role of workplace strategies, processes, and environment has been proven in stimulating employee job satisfaction, well-being, organizational effectiveness and overall productivity [3,4]. By adhering to stringent quality assurance directives, professional organizations strive to ensure that workplaces prioritize factors such as ergonomic design, adequate rest intervals, and access to healthcare services, all of which are essential components of promoting a healthy and sustainable work environment [5]. Work-related musculoskeletal disorders are the most common occupational disorders worldwide [6]. Neck pain (NP) is a major health problem in office workers with a one-year prevalence of 58% among data processing workers, and 33% among other office workers in the UK [7], and of 69% in Belgium [8]. Office workers have been reported to have a higher incidence of chronic pain and transition to persistent or recurrent NP over a one-year period [9]. This disorder is responsible of disability, impaired quality of life (QoL) and QoWL, with a great socioeconomic burden [10,11]. Recognizing the prevalence and the burden of this issue in modern office settings, professional organizations are implementing targeted strategies to address concerns and provide necessary support. These interventions may include ergonomic measures to optimize workstation setups, regular breaks, educational initiatives, and exercises [12].

A considerable number of studies focusing on the effects of exercise for NP in office workers have been conducted [13,14]. The evaluation of the effectiveness of various therapeutic interventions in and out the workplace, aiming to prevent or alleviate NP has been reported, including proprioceptive exercises, stretching, and dynamic-resisted strengthening exercises [15–17]. Until early June 2025, best evidence suggests that self-management for NP is recommended to include education and reassurance along with regular exercise and advice to maintain daily activities [18,19]. It has been proven that self-exercises focusing on strength and endurance training, as well as self-mobilization, were effective in reducing pain and improving function and QoL in NP patients [20]. Adherence to rehabilitation self-exercises poses a significant challenge in managing NP [21]. Patients often struggle to consistently follow prescribed exercise regimens due to factors such as lack of motivation, forgetfulness, or the perceived complexity of the exercises [22]. This non-adherence can hinder the effectiveness of rehabilitation programs and impede patients’ progress toward recovery [22]. Recognizing the need for innovative solutions, a growing interest is in incorporating new tools, such as artificial intelligence (AI) embedded smartphone application (app), into rehabilitation strategies [23]. These apps offer a promising avenue to enhance adherence by providing personalized and interactive exercise programs [24]. They represent a mode of information delivery that is suited to the information technology literate population who are familiar with and frequent users of information technology devices [25], and can be particularly useful in a working population where it may be difficult to find time to attend physiotherapy or educational sessions. While previous studies have explored the effectiveness of self-directed exercises for NP [20], some have made a direct comparison between traditional self-directed methods and smartphone-guided interventions [26]. Notably, a pilot randomized experiment comparing posture correction exercises from brochures and neck workouts from apps was carried out by Lee et al. [26]. The aforementioned study was constrained, nevertheless, by its small sample size (n = 20) and the absence of follow-up evaluations for primary and secondary outcomes, which were only assessed at baseline and just after the intervention [26].

Smartphone-guided exercises offer a potential solution by providing personalized guidance, real-time feedback, and increased motivation, which may lead to improved adherence and clinical outcomes. Thus, the use of a smartphone app to deliver a self-managed exercise and education program for office workers with chronic NP may be effective, demonstrating organizations commitment to safeguarding the health, QoL and QoWL of workers in today’s (***i.e.,*** June 2025) digitally driven workplaces.

### Objective

The objective of this study is to explore the differences in self-management using two workplace-based interventions: a smartphone app consisting of personalized neck exercises compared to conventional approach (***i.e.,*** self-exercises program on paper) in chronic NP office workers. We hypothesize that a smartphone app offering personalized neck exercises will provide superior immediate and short-term improvements in pain relief, functional ability, and QoL for office workers with chronic NP compared to conventional self-rehabilitation methods. Additionally, this approach is anticipated to address the challenge of adherence to self-exercise routines in managing this chronic condition.

### Trial design

A single blinded two-armed randomized controlled trial will be conducted. Participants will be assigned randomly to either the interventional group (IG), utilizing the smartphone app, or the control group (CG).

Fig 1 details the schedule of enrolment (Recommendation for interventional Trials).

**Fig 1 pone.0329863.g001:**
[figure not shown]
Participants timeline: schedule of enrolment, interventions, and assessments (Recommendation for interventional Trials (SPIRIT)). SF12: Short form-12. W: Week.

Fig 2 lists the flowchart of the study design according to “consolidated standards of reporting trials” guidelines [27].

**Fig 2 pone.0329863.g002:**
[figure not shown]
CONSORT (consolidated standards of reporting trials) follow diagram of the progress through the phases of a parallel-randomised trial of two groups. app: Application. NDI: Neck disability index. PI-NRS: Pain intensity number rating scale. QoL: Quality of life. SF12: Short form 12.

## Methods: Participants, interventions, and outcomes

### Study setting

The study will be conducted at the University of Monastir (Tunisia). The latter is a public administration having 70 office workers, with an average (minimum-maximum) age of 45 (30–63) years, possessing an average work tenure of 15 years, engaging in eight hours of desk and computer work daily, five days a week.

### Recruitment

To recruit participants for the trial, a comprehensive digital survey will be distributed to office workers to identify individuals experiencing NP from September 1 to October 30, 2025. The survey clearly explains the trial and its objectives and expresses that all information will be analyzed with strict respect to anonymity, confidentiality, and medical secrecy. By ticking a checkbox, individuals will express their voluntary commitment to join the study, and will have access to questions identifying general information (***e.g.,*** age, sex, comorbidities, work seniority, average number of daily hours spent in front of computer); the existence of NP, duration of symptoms, pain intensity, which will be evaluated via a pain intensity number rating scale (PI-NRS), medication (***e.g.,*** pain killers, physiotherapy). Individuals identified as potentially suffering from this condition will subsequently be invited to undergo a thorough physical examination by a specialist in the field (*SS* in the authors’ list) to confirm the diagnosis.

### Eligibility criteria

Inclusion criteria will be the presence of a chronic NP lasting for more than three months, and a PI-NRS pain level at baseline assessment ≥ 3. Non-inclusion criteria will be acute NP, specific causes of NP (***e.g.,*** chronic inflammatory diseases), spine trauma or surgery, cervical radiculopathy or myelopathy, and physical therapy treatments in the last six months before baseline assessment.

### Informed consent

One researcher (*SS* in the authors’ list) will obtain written informed consents from all eligible participants before allocation. Participants will be clearly informed about the study aims and potential benefits, and that they will be free to withdraw the study at any point with no need to give any specific reason for that. They will be asked if they agree to the use of their data. This trial does not involve collecting biological specimens for storage.

### Intervention

#### Explanation for the choice of comparators.

The so-called conventional approach (self-exercises program on paper) is a standard treatment protocol for self-management in individuals with NP. The exercises are listed in a paper sheet and consist of stretching, strengthening and postural exercises.

#### Intervention description.

All participants of the IG and the CG will receive an educational session explaining the intervention details and an initial training session on how to perform exercises along with advices on proper position and ergonomics to be applied during daily work (***i.e.,*** ensure your workstation setup promotes good posture, with the monitor at eye level and the keyboard and mouse positioned close to your body; take regular breaks from sitting, standing, or staring at screens to stretch and move around). Participants will be instructed to carry out exercises at the same time daily, three to five days per week for 12 weeks.

For the CG, the rehabilitation program is delivered on a paper sheet containing pictures of exercises with a written explanation in French language with the number of sets and repetitions. Participants assigned to the IG will use the smartphone app. The latter includes the rehabilitation program with a detailed explanation in French language with the number of sets and repetitions.

Based on the findings of some papers [13,14], which focused on the effectiveness of exercise interventions for office workers with NP, we selected sets of self-exercise program with detailed explanation suitable for this population (Table 1).

**Table 1 pone.0329863.t001:** Neck self-exercises program.

Items	Description
** *Stretching exercises* **	.***Neck flexion stretch***: Sit tall in a chair; gently lower your chin towards your chest until you feel a stretch in the back of your neck. Hold for 30 seconds and repeat 3 times. .**Neck extension stretch**: Sit tall in a chair; gently tilt your head backward, looking towards the ceiling until you feel a stretch in the front of your neck. Hold for 30 seconds and repeat 3 times. .**Side neck stretch**: Sit tall in a chair; gently tilt your head towards one shoulder until you feel a stretch on the opposite side of your neck. Hold for 30 seconds and repeat on the other side. Repeat 3 times on each side
**Strengthening exercises**	.***Neck retraction exercise***: Sit tall in a chair with your back straight. Gently retract your neck by pulling your chin back without tilting your head up or down. Hold for 5 seconds and repeat 10 times. .***Isometric neck strengthener***: Place your hand against your forehead and push your head forward while resisting with your neck muscles. Hold for 10 seconds and repeat 10 times. Repeat with your hand on the back of your head (pushing backward), and on each side of your head (pushing sideways).
**Postural exercises**	.**Chin tucks**: Sit tall in a chair with your shoulders relaxed. Gently tuck your chin in towards your chest, as if making a double chin. Hold for 5 seconds and repeat 10 times. .**Shoulder blade squeeze**: Sit or stand tall with your arms by your sides. Squeeze your shoulder blades together as if trying to hold a pencil between them. Hold for 5 seconds and repeat 10 times.

### Description of the developed smartphone app

The smartphone app is designed using Android Studio and Flutter. It integrates advanced features, including an intuitive interface and an easy-to-use solution for all users (***i.e.,*** patients and healthcare professionals). Each participant in the IG will receive a code and password to log into the app and to register some general information such as age and sex. All assigned authentications will be recorded in a database created by Firebase. The app features several integrated modules:

(i) Basic information about NP and ergonomic advice on proper neck position during daily work,(ii) Series of evaluation questions including pain assessment (PI-NRS) and the impact of NP on participant’s daily functioning,(iii) Appropriate sets of exercises with videos and instructions,(iv) Daily reminder feature to prompt users to engage in their prescribed exercises consistently, and(v) Evaluation report providing feedback on user’s state and tracking their adherence.

To record participants’ engagement with the program, adherence will be monitored using a user activation tracking system assessing the frequency and duration of app use. The application is linked to the Cloud and Firebase tool enabling the therapist to visualize participants’ results in a graphical form. Exercises included are automatically adapted at each use of the app according to the participant’s condition and evolution. Indeed, the app is designed to analyze the data collected before each use from the evaluation questions based on an AI algorithm and to provide personalized exercise recommendations. To monitor and ensure participant engagement, app usage analytics will be utilized to track interaction patterns and identify any drop-offs in usage. Participants will also have access to technical support to troubleshoot any issues with the app, ensuring minimal disruption. Additionally, scheduled check-ins with participants will be conducted to address potential barriers to engagement and encourage continued adherence to the intervention protocol.

The diagram block (Fig 3) illustrates the app, which is composed of distinct therapist and participant interfaces.

**Fig 3 pone.0329863.g003:**
[figure not shown]
Smartphone application diagram block.

### Criteria for discontinuing or modifying allocated interventions

Any requests from potential participants to discontinue participation in the intervention or follow-up will be accommodated without requiring any explanations.

### Strategies to improve adherence to interventions

Participants of both groups will receive a daily notification on their mobile phone to maximize adherence. Participants using the Smartphone app will have access to relevant information, previously described (***e.g.,*** participant evolution) to encourage them to continue with the proposed protocol.

### Relevant concomitant care permitted or prohibited during the trial

Participants will not be allowed to participate in other trials during the study period. They will be asked not to receive any extra intervention for NP during the intervention period including physiotherapy. They will be instructed to avoid using pain medication; however, if they will do, they will be asked to report the type and frequency of usage. The frequency of pain medication use before and after the intervention will be tracked to offer a more detailed understanding of pain relief and the effectiveness of the intervention.

### Outcomes

The main outcome measure is pain intensity, evaluated according to the PI-NRS [28–30]. The latter is a commonly used tool to measure a person’s pain intensity [28–30]. It is simple, quick, and widely accepted in both clinical and research settings [28–30]. Participants will be asked to indicate their current level of pain on a line from 0 (no pain) to 10 (unbearable pain) [28–30].

Secondary outcome measures are function (***i.e.,*** neck disability index (NDI)), QoL and participants’ adherence to self-exercises. The French validated version of the NDI will be used to assess the impact of NP on individual’s daily functioning [31]. The scale consists of a set of questions addressing various aspects of NP and its influence on activities such as personal care, lifting, reading, working, and recreation. Participants will be asked to rate their level of disability or limitation on a scale for each activity. The total score provides a quantitative measure of the perceived disability associated with NP, with higher scores indicating greater impairment [32]. The French validated version of the short form 12 (SF-12) will be used to measure health-related QoL. The SF-12 is a shorter version of the short form 36, which assesses an individual’s physical and mental well-being. The SF-12 is often utilized in health research, clinical practice, and population health studies [33,34]. Adherence will be measured via two methods. First, it will be evaluated using a frequency-based response scale (***i.e.,*** never, seldom, often, almost always, and always) adapted from the adherence scale of Sluijs et al. [35]. Adherence will then be treated as a dichotomous variable (***i.e.,*** adherent or not adherent), participants who will report “always” or “almost always” will be considered adherent [21]. Second, adherence will be measured based on the frequency of exercise sessions completed. Participants who engage in exercises three or more times per week will be categorized as demonstrating “full adherence” whereas those who exercise twice per week or less will be considered to exhibit “partial adherence”. These combined methods ensure a comprehensive evaluation of adherence, capturing both self-reported behavior and objective frequency of exercise.

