### Sample size

The null hypothesis [36] was H_0_: m_1_ = m_2_, and the alternative hypothesis was H_a_: m_1_ = m_2_ + d, where “***d***” is the difference between two means and n_1_ and n_2_ are the sample sizes for the interventional and control groups, such N = n_1 _+ n_2_. The sample size was estimated using the following predictive equation [36]: $\text{n}\;=\;[\text{2}\;{\text{s}}^{\text{2}}\;{\left({\text{Z}}_{\text{1}-\alpha /\text{2}}\;+\;{\text{Z}}_{\text{1}-\beta }\right)}^{\text{2}}]/{\text{d}}^{\text{2}}$, where

“***n***” is the number of participants;“***Z***_***1-α/2***_” is the normal deviate at a level of significance (type I error at 2-sided = 1.96 at 5% level of significance);“***Z***_***1-β***_” is the normal deviate at 1-β% power with β% of type II error (0.84 at 80% statistical power);“***d***” is the expected difference between average changes of PI-NRS from two groups; and“***s***” is the common variance (standard deviation) of PI-NRS means of two groups. “***s***” was calculated according to the following formula [36]: ${\text{s}}^{\text{2}}\;=\;[({\text{n}}_{\text{1}}-\text{1x}\;{{\text{s}}_{\text{1}}}^{\text{2}}\;+\;({\text{n}}_{\text{2}}-\text{1})\;\text{x}\;{{\text{s}}_{\text{2}}}^{\text{2}}]/({\text{n}}_{\text{1}}+{\text{n}}_{\text{2}}-\text{2})$ .

“***d***” and “***s***” values were obtained from a previous South Korean study [37] including 34 patients (17 in the IG and 17 in the CG). The patients in the IG performed exercises using a video-based app system, whereas those in the CG performed exercises using an image- and text- based printout [37]. In-home training was implemented for six weeks in both groups [37]. The NP intensity was measured before and after the intervention via the PI-NRS. Kim and Shin [37] reported that within both groups, the PI-NRS improved significantly after the intervention. At the end of the intervention, PI-NRS’ changes (expressed as means ± standard deviation) for the IG and CG were 2.23 ± 1.85 and 1.65 ± 1.26, respectively (“***d***” is therefore equal to 0.58 (0.58 = 2.23 - 1.65). Based on the aforementioned study [37], where n_1_ = 17, n_2_ = 17, s_1_ = 1.85, s_2_ = 1.26, “***s***^***2***^” is equal to 2.51 [2.51= [(17-1) x 1.85^2^ + (17-1) x 1.26^2^]/(17 + 17-2)].

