### Statistical methods

All data will be analyzed using SPSS version 23. The Shapiro-Wilk test will evaluate the normal distribution of quantitative data. If the distribution will be normal and the variances are equal, the quantitative data will be reported as mean ± standard deviation, and 95% confidence interval. Otherwise, data will be expressed as median (interquartile range). Categorical data will be expressed in percentage frequencies. The between-group differences in the mean changes of the outcome measures (PI-NRS, NDI, SF-12, adherence) after intervention will be calculated using repeated measures mixed models with participants from the IG as random effect, and group (IG or CG) and time (baseline, four weeks, and 12 weeks) as fixed effects, and with adjustments for baseline imbalance. The Spearman rank test or Pearson product-moment correlation coefficient analysis will be used to analyze the associations between clinical data and mean changes in the outcome measures. Two-sided statistical significance is set at a p value < 0.05.

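### Cheap improvement: compare the groups on the full five-level adherence rating rather than on adherent / not adherent

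*Protocol article*

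**What the plan says.** The Outcomes section of the protocol article names adherence as a secondary outcome and measures it in two ways.

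- **Rating.** Participants answer on five ordered levels, from *never* to *always*. The section then says: "Adherence will then be treated as a dichotomous variable". The top two levels count as adherent and the lower three as not adherent. One literature reference supports this cut.
- **Session frequency.** "Participants who engage in exercises three or more times per week will be categorized as demonstrating “full adherence"; two or fewer sessions a week is called partial. The Intervention description prescribes exercise "three to five days per week for 12 weeks", so this threshold is the lower end of the prescription.

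The Statistical methods section puts adherence in one list with pain, disability and quality of life. All four are compared through mean changes in repeated measures mixed models. The section does not say whether the five-level or the two-category rating enters, and it names no ordinal or binary model. No expected adherence rate, effect or power for adherence is given.

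The Objective ties adherence to the purpose of the trial: "this approach is anticipated to address the challenge of adherence to self-exercise routines".

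**The concern.** The five levels carry an order, and the cut discards most of it. A participant who moves from *never* to *often*, or from *almost always* to *always*, counts as unchanged. If the app raises adherence across the whole scale, part of that effect falls within the pooled categories and the comparison cannot use it.

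The trial is small, and adherence is one of its stated expectations. A less sensitive comparison makes it more likely that a real shift goes unreported. The data for the more sensitive one are already collected.

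The choice of the two-category variable is written into the article, so it is not a detail left to an unseen analysis plan. The form of the model might be specified there. As printed, though, a mean-change analysis fits a two-category variable poorly, and the Outcomes and Statistical methods sections need to be reconciled.

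**Working it through.** **1. Number per arm, from the Sample size section.** The inputs are standard deviations 1.85 and 1.26 with 17 per group, d = 0.58, and z values 1.96 ("type I error at 2-sided = 1.96 at 5% level of significance") and 0.84 ("0.84 at 80% statistical power").

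- s² = (16 × 1.85² + 16 × 1.26²) / 32 = 80.16 / 32 = 2.505
- n = 2 × 2.505 × (1.96 + 0.84)² / 0.58² = 39.28 / 0.3364 = 116.8, rounded to 117
- n′ = (70 × 117) / (70 + 117) = 8190 / 187 = 43.8, rounded to 44
- 44 / 0.9 = 48.9, planned as 50 (25 per arm)

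The plan's figures reproduce. Its evaluable number is 44, or 22 per arm. I take that number as given and do not assess here how it was reached.

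**2. Assumptions, none of them from the documents.** These are the control distribution over the five levels and a common odds ratio OR for the app at every level (proportional odds). The adherent share in the app arm follows as

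p_app = OR × p_c / (1 − p_c + OR × p_c).

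For OR 4:

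- p_c = 0.25: 1.00 / 1.75 = 0.571
- p_c = 0.40: 1.60 / 2.20 = 0.727
- p_c = 0.65: 2.60 / 2.95 = 0.881

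**3. Power by simulation.** This is a single-visit comparison with 22 per arm at the plan's level ("Two-sided statistical significance is set at a p value < 0.05"). The full rating is compared by a tie-corrected Wilcoxon test and the cut rating by an uncorrected chi-square test.

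| OR | Control adherent | Full rating | Cut rating | Loss (points) |
|---|---|---|---|---|
| 4 | 25% | 70% | 58% | 12 |
| 4 | 40% | 70% | 60% | 10 |
| 4 | 65% | 67% | 45% | 22 |
| 5 | 30% | 81.9% | 73.5% | 8.5 |
| 5 | 40% | 82.2% | 71.3% | 10.9 |
| 5 | 50% | 80.4% | 65.7% | 14.7 |
| 5 | 65% | 78.6% | 54.3% | 24.4 |

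Over OR 3 to 5 and control shares of 25 to 65%, the loss is about 8 to 24 points. At OR 2 it is about 4 to 7 points. With no effect, the Wilcoxon test rejected in 4.5 to 5.2% of runs and the chi-square test in 4.5 to 6.4%, so the gain does not come from a liberal full-scale test.

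**4. Sensitivity.**

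- *More adherent controls.* At 75% adherent and OR 5, power is 76.3% against 42.3%, a loss of 33.9 points.
- *Fisher's exact test on the cut.* At OR 5 and control shares of 20 to 65%, the loss is about 20 to 37 points.
- *Effect only across the cut.* Take control shares of 0.10, 0.20, 0.35, 0.25, 0.10 and app shares of 0.10, 0.20, 0, 0.60, 0.10. The adherent share rises from 35% to 70%. The rank test then has 25.5% power and the cut test 65.7%, so the cut is better by about 40 points.

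**The case against.** The strongest reply has four parts.

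**The size is assumed.** No adherence rate or effect is in the protocol, and proportional odds is the model under which a Wilcoxon test does well. This stands. The figures are illustrations, and the direction reverses if the effect lies only at the cut. A broad shift remains the more natural expectation, since the Discussion describes an app that adapts intensity, frequency and duration and improves adherence generally.

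**The comparison is not the planned model.** The calculation uses one visit, whereas the plan uses repeated measures and does not say which form of the variable enters. This also stands. It means the two sections need reconciling; it does not show that the full rating will be used.

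**The session threshold is sensible.** A reader might infer that the three-per-week cut is equally faulty because three and five days look the same. The documents do not support that. Three days already meets the prescription, so the category separates those who reached the prescribed minimum from those who did not. A raw count could also mix app-set frequency with adherence, because the app may change frequency. Nor does the article state that a numeric weekly count is collected in the control arm: participants rate their adherence in a questionnaire, and usage tracking is described for the app.

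**It is a secondary outcome with no power claim, and the rating cut has a cited source.** This is fair. The point concerns efficiency, not bias or error.

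**Conclusion.** The point holds as a cheap improvement for the five-level rating. The protocol states the cut and plans no analysis of the uncut rating, and its mean-change mixed model is not described in a form that suits either version.

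The illustrative cost is about 8 to 24 points of power for OR 3 to 5, and about 4 to 7 points for OR 2. This rests on 22 per arm, 25 to 65% of controls adherent, a proportional-odds shift, a single visit and a chi-square test on the cut. Other inputs give other losses, and an effect confined to the cut gives a gain.

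A reader might infer that the trial will lose a known amount of power, or that it will miss an adherence benefit. Neither follows, because the documents contain nothing from which adherence power could be fixed. The session-frequency category is not a fault.

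**What to change.** In the Outcomes and Statistical methods sections:

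- Make the between-group comparison of the full five-level rating the main adherence analysis, by a proportional-odds model or a Wilcoxon test at week 12, and at week 4.
- Keep the percentage adherent as a descriptive or supportive result.
- State which form of adherence enters which model, and take adherence out of the mean-change list unless a suitable model is named.
- Keep full / partial for session frequency. Add a comparison of the weekly number as supportive only if the same self-reported count is collected in both arms.

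**Cost.** For the rating this is a change of wording with no new data. An odds ratio or rank shift is less simple to report than a percentage, which stays available. For sessions, a common count may need a questionnaire item that the article does not describe, and the count may reflect app-set frequency as well as adherence. The change should be fixed before outcome data are examined.

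### The session-count adherence measure has no non-adherent class, so participants who do no exercise are reported as partially adherent

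*Protocol article*

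**What the plan says.** Adherence to the self-exercises is one of three secondary outcomes in the protocol article, with function and quality of life (Outcomes). It is measured in two ways.

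- **Self-rated scale.** There are five possible answers: "never, seldom, often, almost always, and always". The scale is then split in two: "participants who will report “always” or “almost always” will be considered adherent". The other three answers are by implication not adherent.
- **Session count.** "Second, adherence will be measured based on the frequency of exercise sessions completed". The upper class is "Participants who engage in exercises three or more times per week will be categorized as demonstrating “full adherence". For the lower class the text continues "whereas those who exercise twice per week or less will be considered to exhibit “partial adherence". No third class is given here or elsewhere in the article.

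The prescription against which adherence is judged is "three to five days per week for 12 weeks" (Intervention description). The Objective section states that "this approach is anticipated to address the challenge of adherence to self-exercise routines". The Outcomes section presents the two measures together as a comprehensive evaluation of adherence.

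**The concern.** A class defined as two sessions per week or fewer includes zero. Read as written, a participant who stops in the first week and one who exercises twice every week receive the same label, and that label credits both with some adherence.

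This matters because non-adherence is part of the trial's rationale. The Introduction describes it as a challenge that can hinder rehabilitation, and the Objective and Discussion expect the app to help with it. A reader of the results would want to know how many people in each arm did nothing. The session count cannot say, and its label suggests the answer is nobody.

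The article states these cut-offs and labels itself, so this is a rule already fixed and not a detail left to an analysis plan.

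**Working it through.** The plan gives no figure to reproduce here. The check is to apply the two written rules literally and see where each participant falls.

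**Inputs (all from Outcomes unless noted)**
- Session count: 3 or more per week = full; 2 or fewer per week = partial.
- Self-rated scale: always or almost always = adherent; never, seldom or often = not adherent.
- Prescribed minimum: 3 days per week (Intervention description).
- Arm size: 25 per group (Sample size).

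**Step 1. Session-count rule applied to each weekly frequency**

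| Sessions per week | Class as written | Class under the proposed fix |
|---|---|---|
| 0 | partial | non-adherent |
| 1 | partial | partial |
| 2 | partial | partial |
| 2.5 (only if averaged) | none | partial |
| 3, 4, 5, 7 | full | full |

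No frequency leads to a non-adherent class under the written rule.

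**Step 2. The two measures side by side.** A participant who does no exercise and answers never is not adherent on the scale and partially adherent on the count. A participant who answers often is also not adherent on the scale. The not-adherent class on the scale therefore mixes never, seldom and often, while the partial class on the count mixes 0, 1 and 2 sessions. Neither derived variable separates out those who did nothing.

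**Step 3. How much the lower class can hide.** Let f be the share with full adherence in an arm. The reported table shows f full and 1 − f partial. The true share with zero sessions can lie anywhere from 0 to 1 − f without changing that table. The documents do not give f, so these values are assumptions:
- f = 40%: 10 of 25 full. Between 0 and 15 of 25 (0% to 60%) could have done nothing.
- f = 60%: 15 of 25 full. Between 0 and 10 of 25 (0% to 40%).
- f = 80%: 20 of 25 full. Between 0 and 5 of 25 (0% to 20%).

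In every case the session count reports no one as non-adherent.

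**Step 4. Full against the rest.** Under three classes the rest is partial plus non-adherent, which again sums to 1 − f. For anyone the written rule already classifies, this comparison is the same before and after the change.

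**Step 5. Averaging.** If frequency is summarised as a mean over weeks, a participant alternating 2 and 3 sessions over four weeks has (2 + 3 + 2 + 3)/4 = 2.5. That is below the upper class and above the lower one. If the participant instead reports a usual whole number of sessions per week, the gap does not arise. The article does not say which applies.

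**The case against.** The best defence is that the cut at three sessions is sensible. It matches the prescribed minimum, so the measure asks whether the participant met the prescription, and renaming the lower class would not alter that comparison. The self-rated scale sits beside it and has a not-adherent class. The app also tracks frequency and duration of use to identify drop-off (Description of the developed smartphone app). Finally, two instruments that label the same person differently do not in themselves contradict each other.

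Most of this stands, and it limits the point. Several stronger readings should be resisted:

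- A reader might infer that the trial cannot report non-adherence at all. That holds only for the session count; the self-rated scale can report it. The raw answer never is also collected, so it could be tabulated, although no defined variable does so.
- A reader might infer that a real benefit of the app would be missed. One can construct such a case: 40% full in both arms, with 30% at zero sessions in the control arm against 5% in the app arm. The count then shows no difference, while abandonment differs by 30 − 5 = 25 points. The result follows from placing the whole difference below the cut, and nothing in the documents supports those percentages.
- A reader might take the gap between 2 and 3 as a definite error. It is conditional on averaging, which the text does not state.

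The defence does not remove the core defect. The app's usage tracking covers one arm only, and the scale pools never with seldom and often. The partial label is still wrong for someone with zero sessions.

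**Conclusion.** The point holds in a limited form. As written, the session-count measure reports participants with no sessions as partially adherent, has no non-adherent class, and cannot separate abandonment from one or two sessions per week. The self-rated measure mitigates this only in part.

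The harm lies in the description and reporting of one of two measures of a secondary outcome. The primary outcome, the sample size and any comparison of full adherence with the rest are unaffected. The share hidden in the lower class cannot be estimated from the documents; it is bounded only by the share not fully adherent.

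The mislabelling rests on the plain wording and needs no assumption. The gap between 2 and 3 assumes that frequency is averaged over weeks. The definition should be corrected before adherence data are analysed.

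**What to change.** Keep the threshold of three and redefine the session-count classes over each assessment period (baseline to week 4, and week 4 to week 12) so that they are mutually exclusive and exhaustive:

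- full: 3 or more sessions per week;
- partial: above 0 and below 3 sessions per week;
- non-adherent: 0 sessions in the period.

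Non-adherent should mean zero sessions in the period and nothing else. Adding participants who stopped part-way would make it overlap with the partial class. State whether the frequency is a mean over the period or a usual weekly number.

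Also report sessions per week itself by arm, obtained in the same way in both arms, for example by an item in the existing 4- and 12-week digital questionnaire. Usage tracking is described only for the app arm, and the article names no diary or log for the paper arm. Comparing tracked counts with recalled ones would confuse the source of the data with the effect of the app.

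The cost is a revised definition, one more category to report and, unless the questionnaire already asks for a number of sessions, one added item. The comparison would rest on self-reported frequency in both arms, with app tracking kept as supporting information for the app arm.
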